### Interim analyses {21b}

One interim analysis is to be performed when 39 patients had been enrolled. The investigators performed the analyses according to methods described in the statistical plan to ensure the robustness and validity of the analyses.

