### Sample size {14}

This study is a randomized controlled trial with botulinum toxin injections in the experimental group and glucocorticoid (tretinoin acetate) injections in the control group. The main regression indicator observed is the VAS pain score.

In this study, the sample size will be calculated with reference to similar relevant literature and pre-experimental results. The sample size will be calculated using two independent sample mean validity tests using the G-Power version 3.1.2 software. It is assumed that the means of the two groups are equal at baseline, that there is a 1-point difference in VAS pain score between the two groups at the first post-treatment assessment, and that the standard deviation of the two groups was 1.4, which should be consistent at each subsequent assessment, measured as an effect size (i.e., Cohen *d*, 0.71). Based on these magnitudes, alpha = 0.05 two-tailed is set. To achieve 80% efficacy, 32 patients per group will be counted as study subjects. To compensate for potential loss to follow-up, approximately 20% of patients will be added, with a final inclusion target of 78 patients (39 in each group).

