## Assignment of interventions: blinding

### Who will be blinded {17a}

This trial is a double-blind design, with subjects and investigators (including outcome measures and statisticians, etc.) not aware of the grouping. The physician who injected the drug is unblinded in this trial as the test drug used in this trial is a colorless, clear liquid with a different appearance to the cloudy glucocorticoid liquid used in the control group. This physician is not involved in the rest of the trial and must be out of the view of the subject and investigator when preparing the drug and injecting it.

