## Statistical methods

### Statistical methods for primary and secondary outcomes {20a}

All statistical inferences will be performed by two-sided test, the test level of statistical significance is set as 0.05, and the confidence interval of parameters is 95%. The count data describe the number of cases and percentage, and the measurement data describe the mean, standard deviation, minimum, maximum, median, and 25th and 75th quantiles. The counting data give the frequency distribution and the corresponding percentage. Qualitative data give the number of cases of positive rate, positive number, and denominator.

Shapiro–Wilk test will be used to verify the normality of the variables. For normally distributed variables, continuous variables are represented by “mean ± standard deviation”; for data that is not normally distributed, it is represented by “median, interquartile.”

In the analysis of baseline data, the independent sample *t* test will be used to compare the normal distribution between the measurement data groups. The non-normal distribution data are presented with median and interquartile intervals. Mann–Whitney *U* test will be used to compare ordered categorical variables between groups.

Repeated measures ANOVA will be used to study the independent effects, main effects, and interactions of time and grouping. *p* < 0.05 is considered statistically significant. Intentionality and protocol sets will be used to analyze primary and secondary outcomes. The results of intentionality treatment analysis are compared with those of protocol set analysis to determine whether the results are consistent. Missing data are processed as multiple imputation. Adverse events will be listed and analyzed using chi-square tests or Fisher precision tests. We analyzed test results using the IBM SPSS24.0 software.

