### Composition of the data monitoring committee, its role and reporting structure {21a}

A data monitoring committee is not required because of the short duration of our trial and the known low risks. But researchers will regularly analyze the data and make adjustments.

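### The protocol plans one interim analysis, then also commits the researchers to regular analyses with adjustments; neither is reconciled with the single 0.05 level, the fixed-design sample size or the blinding

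*Protocol article*

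**What the plan says.** All references are to the protocol article.

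- **Interim analyses {21b}:** "One interim analysis is to be performed when 39 patients had been enrolled". On who does it and how: "The investigators performed the analyses according to methods described in the statistical plan". The section gives no purpose, endpoint, boundary or stopping rule.
- **Data monitoring committee {21a}:** "A data monitoring committee is not required because of the short duration of our trial and the known low risks". The next sentence reads: "But researchers will regularly analyze the data and make adjustments". It gives no number, content or limit, and refers to no plan.
- **Statistical methods {20a}:** "All statistical inferences will be performed by two-sided test, the test level of statistical significance is set as 0.05". No other level appears anywhere in the article.
- **Sample size {14}:** "alpha = 0.05 two-tailed is set", in a two-group comparison of means with 32 evaluable patients per group for 80% power, raised to 39 per group. No part of the 0.05 is set aside for an earlier test.
- **Who will be blinded {17a}:** "investigators (including outcome measures and statisticians, etc.) not aware of the grouping".
- **Plans for assessment and collection of outcomes {18a}:** the analysis is given to a statistical analyst, and allocation is to stay blinded.

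**The concern.** Three things do not fit together.

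1. **Number of looks.** One section plans a single interim analysis. Another commits the researchers to analyses at regular intervals. A reader cannot tell how often the accumulating data will be examined.
2. **Significance level.** The general level is 0.05 and the trial is sized to use all of it once, at the end. If an earlier look also compares the groups at 0.05 and its result can be acted on, the chance of a false positive claim on the primary outcome exceeds 5%.
3. **Who looks, and what follows.** The people named are the investigators and the researchers, there is no independent body, and adjustments are foreseen. If results by group, even under coded labels, reach the people who recruit or assess, the emerging difference can influence recruitment and the ratings. The primary outcome is pain reported by the patient to an assessor, so this matters here.

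**Working it through.** **Step 1. Reproduce the plan's sample size.** Inputs from Sample size {14}: difference 1 point, SD 1.4, two-sided 0.05, power 80%. The effect size is d = 1/1.4 = 0.714. The two-sample t test (noncentral t) needs 31.76 per group, so 32, with power 80.3%. Adding 20% gives 32 × 1.2 = 38.4, so 39 per group and 78 in all. The stated figures reproduce, and they are those of a fixed design with one test at the full 0.05.

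**Step 2. Place the look.** 39/78 = 0.50 of the target. The trigger counts enrolled patients, not patients with 4-week data, so the information fraction is at most 0.50.

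**Step 3. Type I error if the look and the final analysis both test efficacy at 0.05 and either can support a claim.** With information fraction t, the two test statistics are bivariate normal under the null with correlation √t. At t = 0.50 the correlation is 0.707, and

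P(|Z₁| > 1.96 or |Z₂| > 1.96) = 0.0831, or 8.3%.

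At t = 0.45 it is 8.5%, and at t = 0.40 it is 8.6%.

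**Step 4. Further looks.** The article does not say how many regular analyses there will be, so the number is an assumption. The values below are for equally spaced efficacy tests at 0.05, counting the final one (the two-look value is exact, the rest are simulated with 1,000,000 draws).

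| Total looks (assumed) | Overall type I error |
|---|---|
| 2 | 8.3% |
| 3 | 10.7% |
| 5 | 14.2% |
| 10 | 19.3% |
| 18 (about monthly over the planned 18-month recruitment) | 23.9% |

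**Step 5. The other end of the range.** If no look compares the groups, and none can lead to a claim, a stop or a change driven by the group difference, the final test at 0.05 keeps its 5%.

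**Step 6. How likely the missing rule is to matter.** Under the planned effect, the chance of p < 0.05 at the interim is about 58% if all 39 have outcome data (19 and 20 per group). It is about 50% with 16 per group, which is half of the 32 evaluable per group. A nominally significant interim result would be an ordinary event if the effect is as planned.

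**Step 7. What a boundary would cost.** For two looks at t = 0.50 and 1, O'Brien-Fleming bounds are z = 2.797 (nominal p 0.0052) and z = 1.977 (nominal p 0.0480), and the overall error computes to 0.0500. The final t test at 0.048 with 32 per group has power 79.8%, against 80.3% at 0.05. Counting rejections at either look (normal approximation), the comparison is 81.2% against 81.5% for the fixed design.

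**The case against.** The strongest reply is that the article never says the interim tests efficacy. The 0.05 is a general level in the section on primary and secondary outcomes and does not mention looks. The interim section points to a statistical plan, which is not shown and could contain a boundary, a safety-only review or a pooled look. This stands. A reader might infer that the protocol prescribes 0.05 at every look, and that the true type I error is therefore well above 5%; the text supports neither as a fact. The 8.3% is conditional, and the larger figures also depend on an assumed number of looks.

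A second reply concerns the blind. The section on blinding counts statisticians among the blinded investigators, so an interim done by the investigators may mean one done by the blinded analyst. An analysis of pooled data breaks no blind. This also stands: a reader might infer that the blind is broken, but no section says that anyone will see results by arm. What remains is a risk that the article does not address.

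A third reply is that the regular analyses may be no more than data checks, since audits every 4 weeks are planned under {23}, and that amendments to design or sample size need ethics approval under {25}. This stands only in part. The sentence speaks of analysing data and making adjustments, does not limit itself to checks, and defers to no plan. Ethics approval does not control type I error. A boundary that exists only in the unseen plan would also still have to be squared with the 0.05 stated for all inferences and with the fixed-design sample size.

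**Conclusion.** The point holds as an unreconciled contradiction with a conditional effect on error. The sections on interim analysis and data monitoring disagree on how often the data are analysed. Neither is squared with the blinding, the single 0.05 level or the fixed-design sample size.

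The size depends on what the looks do. Overall two-sided type I error is about 8.3% if the look at 39 is an efficacy test at 0.05 that can lead to a claim, a stop or a change. It is higher if the regular analyses are such tests too, and 5% if no look compares the groups. The article does not settle which case applies. Followed as written, it permits repeated data-driven changes by the trial team, with no independent body and a full 0.05 test at the end. That should be settled before the 39th patient is enrolled.

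**What to change.** 1. **Data monitoring {21a}:** delete the sentence on regular analyses and adjustments, or limit it to blinded data-quality checks and pooled safety review.
2. **Interim analyses {21b}:** state that the look at 39 patients uses pooled, blinded data only (for example overall VAS standard deviation, missing data and adverse events), with no between-group test. The final test at 0.05 then remains valid.
3. **If a comparative look is wanted instead:** state two looks with O'Brien-Fleming bounds, nominal p 0.0052 at half information and 0.0480 at the end. Define half information by patients with outcome data, not by enrolment. Amend {20a} so that its level agrees. Have the look run by a statistician who does not share results by group with anyone who recruits or assesses patients.

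Cost: a wording amendment and no change to the 78 patients. If the comparative look is kept, power at 32 per group is about 79.8% instead of 80.3%.

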### Methods for additional analyses (e.g., subgroup analyses) {20b}

Sub-group analyses are not foreseen.

### Methods in analysis to handle protocol non-adherence and any statistical methods to handle missing data {20c}

Missing data will be addressed using multiple inference methods. Analyses are performed in the imputed datasets, and the results are summarized to ensure that the data are unbiased and the inferences are reliable.

### Plans to give access to the full protocol, participant-level data, and statistical code {31c}

The study protocol and data analysis will be obtained from the corresponding author according to the protocol.

## Oversight and monitoring

### Composition of the coordinating center and trial steering committee {5d}

The ethics committee of Zhujiang Hospital Affiliated to Southern Medical University will supervise the researchers and all levels of the study to ensure that the study follows ethical principles and protects the health of patients.

### Composition of the data monitoring committee, its role and reporting structure {21a}

A data monitoring committee is not required because of the short duration of our trial and the known low risks. But researchers will regularly analyze the data and make adjustments.

### Adverse event reporting and harms {22}

Adverse events for patients will be recorded at each follow-up visit. Adverse events are defined as all negative events of consequence that occur during the trial, regardless of their relationship to the study content, and need to be recorded when they occur. Details of the relevant event will also be recorded and a determination made as to whether it is an adverse event.

We will report and manage adverse events associated with drug injections in detail, mainly induced muscle atrophy. Participants are encouraged to keep a daily training diary to monitor their physical condition. This is a quick way to identify and mitigate any potential hazards.

### Frequency and plans for auditing trial conduct {23}

Our study will have scheduled audits every 4 weeks. The audit included data on participants’ personal information, written informed consent, and primary and secondary assessment scales. In addition, we will carefully review good practice for treatment safety, reporting of adverse events, and completeness and accuracy of data collection. Routine audits reinforced methodological rigor and ethical compliance.

### Plans for communicating important protocol amendments to relevant parties (e.g., trial participants, ethical committees) {25}

Any measures that may affect the study protocol, patient interests, or patient safety need to be modified. This includes aspects such as study objectives, study design, demographics, and sample size. All proposed changes need to be submitted to the Ethics Committee of Zhujiang Hospital Affiliated to Southern Medical University for approval. The revised protocol can proceed only after the necessary ethical approval has been obtained.

### Dissemination plans {31a}

The findings of the study will be released to participants, medical professionals, the general public, and other relevant groups through publications.

## Discussion

This trial is designed to investigate the improvement of shoulder pain after botulinum toxin or glucocorticoid injections in two groups of patients with hemiplegia. Botulinum toxin is a new method of treating neuropathic pain and has shown promising results in the treatment of neuropathic and chronic pain disorders [6, 34]. Some scholars believe that botulinum toxin can inhibit the release of inflammatory transmitters from peripheral sensory nerve endings and indirectly inhibit nociceptive sensitization of nerves [35].

Previous studies have been conducted including the study by Mahowald et al., in 2006, which evaluated the treatment of pain with intra-articular botulinum toxin [36], and the randomized controlled trial comparing intra-articular botulinum toxin injection with placebo [37]. A prospective study in Korea also compared intra-articular injection of botulinum toxin with triamcinolone acetonide for frozen shoulder [37]. Although intra-articular botulinum toxin injection is not a pioneering technique, the innovation of this study is to apply this method specifically to neuropathic pain after stroke and to examine changes in cortical activation by functional NIR spectroscopy. With the help of fNIRS to study the therapeutic mechanism, we applied it to the clinic in order to determine the degree of relief of neuropathic pain after stroke by botulinum toxin and to obtain a more objective criterion for the assessment of rehabilitation. Furthermore, we chose this controlled trial to compare the effectiveness of botulinum toxin and glucocorticoid injection therapy, which provides stronger evidence than comparisons with placebo or no treatment.

For the treatment of HSP, more published literature has injected botulinum toxin into the affected pectoralis major muscle or subscapularis to improve the angle of movement of the patient’s shoulder joint by decreasing muscle tone, thereby reducing pain triggers. It has been suggested that the effect of botulinum toxin on pain is independent of its effect on muscles and acts directly on sensory neurons [38, 39], considering that intra-articular cavity injections can obtain longer-term pain relief [40], which can effectively avoid adverse reactions such as muscle atrophy from injection into muscle tissue. This is the main reason why we chose joint cavity injections as our target.

We will primarily attempt to quantify the relief of the patient’s shoulder pain using VAS. To observe the improvement in pain in relation to the oxyhemoglobin concentration in the corresponding brain regions, we will apply the fNIRS to quantify the corresponding brain regions of the patients. fNIRS is particularly suitable for predicting changes in pain intensity. Quantifying changes in cortical activation associated with nociception by fNIRS. Related studies have also confirmed the involvement of the PFC and S1 brain regions in pain processing [41]. We hoped that changes in blood flow activity in the corresponding brain regions would provide objective data to support shoulder pain relief to complement patients’ subjective report of pain scores. The agreement between subjective perception of pain and objective HbO in subjects measured using fNIRS is more consistent. The Fugl-Meyer assessment examined whether pain reduction improves motor function, an important functional outcome in post-stroke rehabilitation.

A limitation of this study is the lack of a control group receiving sham injections of placebo. The short follow-up period of 4 weeks is another limitation. Long-term outcome data could help assess the durability of injection pain relief. In conclusion, this trial is research to assess the effectiveness and security of ultrasound-guided botulinum toxin injections in the treatment of patients with HSP. The results of this research will be important for clinicians to prescribe as a treatment option, and the scientific and methodologically rigorous design of this trial is expected to provide a reliable reference for the future application.

Future studies could explore intra-articular botulinum toxin injections in combination with rehabilitation programs (e.g., physiotherapy or occupational therapy) to optimize functional outcomes. Other neuroimaging methods, such as fMRI, may also provide further insights into the central mechanisms of hemiplegic shoulder pain.

## Trial status

At the time of submission, this study has completed ethical registration and has not yet started the trial. The protocol version number is 04, and the date is February 13, 2023. The recruitment start date will be March 1, 2024, and the estimated end date will be September 1, 2025.

## Data Availability

Data will be available from the corresponding author upon reasonable request.

## Abbreviations

HSP: Hemiplegic shoulder pain
fNIRS: Functional near-infrared imaging
VAS: Visual analog scale
HBO: Oxyhemoglobin concentration
DLPFC: Dorsolateral prefrontal area
M1: Primary motor area
S1: Primary sensory area
ROM: Passive range of motion
